#### Economic evaluation

The economic evaluation is performed from a societal perspective. The evaluation is a combination of a cost-effectiveness analysis on caregiver's sense of competence (SCQ) and two cost-utility analyses on caregivers and patients separately. Utilities are based on the EQ-5D [57]. Quality Adjusted Life Years (QALY) are calculated by multiplying the utility with the amount of time a patient spends in this particular health state [58]. Incremental costs per QALY gained are calculated. In all analyses, direct costs inside and outside health care are considered. Besides, indirect costs of productivity loss of caregivers and indirect costs of the intervention are estimated. Direct costs inside health care (e.g. costs of consulting the GP, hospitalizations, and use of medication), direct costs outside health care (e.g. costs of traveling, costs of informal care, and costs of consulting alternative health professionals), and productivity loss are assessed by means of cost diaries for caregivers and patients, in which subjects register the amount of healthcare they use. Indirect costs of the intervention, such as nurses' trainings, are calculated using the bottom-up method, by measuring all resources and multiplying these by associated cost prices. Dutch guidelines for economic evaluations in health care are followed to estimate costs [59].

### Sample size calculation

Sample size calculations were based on scores reported for groups similarly to our target group on the main outcome measure of the RCT, namely sense of competence (mean 17.9 SD 5.2, range 4–27) [60]. Calculations are based on α = 0.05 and a desired power of 0.80. For an anticipated effect of 15% difference in final scores between intervention group and usual care group, and with improved scores in the intervention group and stable scores in the control group, 37 persons per group are required. As we expect a drop out rate of about 25% during the one-year follow-up, this means a total of 100 patients and caregivers to be included in the study.

### Blinding

Interviewers are kept blind from the randomization status of participants. GPs can be unaware of patients allocated to the usual care group, but they will be aware of patients in the intervention group as nurses contact the GP about these patients. Participants are not blinded.

### Analysis

#### Effect evaluation

Data are primary analyzed according to the intention-to-treat principle. Additionally, data are analyzed according to the on-treatment (i.e. per protocol) principle in order to examine whether protocol deviations have caused bias. General Linear Models are used to analyze differences between the intervention and usual care group on caregiver's sense of competence, caregiver's quality of life and caregiver's psychological well-being. Potential baseline differences are accounted for by covariates. Differences in days until institutionalization and death between patients of the two groups are tested with survival analyses (Cox-proportional hazard modeling). Differences on patient's hospitalization days and patient's quality of life are tested by a chi-square test and student t-test, respectively. Potential confounding is checked, including the effect of different interviewers and nurses.

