**Methods/design:**

In this randomized controlled trial, effectiveness as well as cost-effectiveness of case-management is evaluated. It concerns case-management in early-detected patients with dementia symptoms and their primary informal caregivers. Participants are followed up to twelve months after baseline assessment. The main outcome measure of the effect evaluation is the caregiver's sense of competence to care for the older person with dementia symptoms. The economic evaluation is performed from a societal perspective.

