An innovative initiative to support dementia patients and their caregivers was set up by the Department of General Practice of the VU University medical center, GPs and district nurses in West-Friesland, the Netherlands. We developed a pro-active program, in which the key elements consist of timely detection of dementia symptoms followed by case-management by district nurses among detected patients and their primary informal caregivers. A randomized controlled trial (RCT) is performed to observe effectiveness and cost-effectiveness of case-management.

The objective of this paper was to describe the study protocol of this RCT among informal caregivers of men and women aged 65 years or over with dementia symptoms who live at home, and the men and women they take care of. The main research questions of this RCT concern whether case-management is more effective than usual care in improving caregiver's sense of competence, and whether case-management is cost-effective compared to usual care when assessed from a societal perspective. A secondary research question is whether case-management is more effective than usual care in improving caregiver's quality of life, caregiver's psychological well-being, caregiver's burden, patient's quality of life, and in decreasing hospital days, days until institutionalization and death of the patients.

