### Measurements

Table 1 provides an overview of all effect and economic measurements. At baseline (T0), and after 6 (T1) and 12 months (T2) trained interviewers visit participants. At baseline and after 6 months, they leave cost diaries for patients and caregivers to register medical consumption during the successive 6 months. These cost diaries also provide the possibility to visualize delivery of the intervention and usual care. When patients are unable to fill out a questionnaire, their informal caregiver is allowed to fill it out or to provide assistance.

**Table 1 T1:** Measurement Scheme

**variable**	**Instrument**	**T0**	**T1**	**T2**

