#### Effect evaluation

Primary outcome is:

1. Caregiver's sense of competence as measured with the Sense of Competence Questionnaire (SCQ) [45].

The SCQ consists of three domains, identified by factor analysis: consequences of involvement in care for the personal life of the caregiver, satisfaction with one's own performance as a caregiver and satisfaction with the impaired person as a recipient of care. The questionnaire was based on Zarit's Burden Inventory [46] and Bengtson and Kuypers' family crisis model [47].

Secondary outcomes are:

2. Caregiver's quality of life by means of the MOS 36-item short-form health survey (SF-36) [48];

3. Caregiver's psychological well-being as determined with the Center for Epidemiologic Studies Depression Scale (CES-D) [49];

4. Caregiver's burden by means of the Self-Perceived Pressure by Informal Care (SPPIC) [50];

5. Days until institutionalization of the patient as checked with GP records;

6. Patient's quality of life as measured with the Dementia Quality of Life Instrument (DQOL) [51];

7. Days until death of the patient as checked with GP records;

8. Hospital days of the patient by means of cost diaries.

Apart from these outcomes, we assess the following potential confounding variables on the level of the caregiver: socio-demographic characteristics, disabilities in activities of daily living (ADL) functioning and instrumental activities of daily living (IADL) functioning by means of the Groningen Activity Restriction Scale (GARS) [52], presence of chronic diseases, locus of control (Mastery) [53], and social support (social support list) [54]. On patient level we assess socio-demographic characteristics, cognitive functioning (MMSE, 7MS, IQCODE), presence of chronic diseases, ADL and IADL disability with the Interview for Deterioration in Daily living activities in Dementia (IDDD) [55], behavioral problems and mood by means of the Neuropsychiatric Inventory (NPI-Q) [56], and incontinence.

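### The chi-square test planned for hospital days does not match an outcome defined as a number of days per patient

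*Protocol article*

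**What the plan says.** Three places define the outcome as an amount.

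- **Background:** the secondary research question asks whether case-management is better than usual care "in decreasing hospital days, days until institutionalization and death of the patients".
- **Measurements – Effect evaluation:** the last secondary outcome is "Hospital days of the patient by means of cost diaries".
- **Table 1:** hospital days of the patient are registered continuously through the cost diaries. On the diaries, the Measurements section says that interviewers visit and "they leave cost diaries for patients and caregivers to register medical consumption during the successive 6 months".

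The test is fixed under Analysis – Effect evaluation: "Differences on patient's hospitalization days and patient's quality of life are tested by a chi-square test and student t-test, respectively". The last word of that sentence ties the chi-square test to hospital days and the t-test to patient quality of life. The article defines no yes/no version, such as any admission, and no grouping of days.

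**The concern.** A chi-square test compares frequencies of categories. To use it on a number of days per patient, someone must first turn the days into categories, and the article does not say how. The choice decides what is tested: the proportion of patients ever in hospital, or whether the arms differ in an unordered list of day values. Neither addresses whether case-management reduces the number of days. A real difference in length of stay could be reported as no difference, and the test yields no estimate of the difference in days. Because the form is not named, it could also be chosen after the data are seen.

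**Working it through.** **Inputs from the article.** Sample size calculation: "Calculations are based on α = 0.05 and a desired power of 0.80"; "sense of competence (mean 17.9 SD 5.2, range 4–27"); "For an anticipated effect of 15% difference in final scores between intervention group and usual care group"; 37 per group; drop-out about 25%; 100 in total. Abstract: "Participants are followed up to twelve months after baseline assessment", taken as 365 days per patient. Two-sided testing is assumed, as sidedness is not stated.

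**The plan's own figure.** The article gives no number for hospital days, so the only figure to reproduce is the group size.
- If 15% means 15% of the scale range, the difference is 0.15 × (27 − 4) = 3.45.
- n = 2 × (1.96 + 0.8416)² × 5.2² / 3.45² = 2 × 7.849 × 27.04 / 11.90 = 35.7, so 36. The t-based version gives 36.65, so 37.
- 37 / 0.75 = 49.3, so 50 per arm and 100 in total.

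The group size is reproduced on that reading, so the check uses 37 and 50 per arm.

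**Assumptions not in the article.** 10–40% of patients are admitted during the year. Mean stay if admitted is 5, 10 or 14 days, drawn as 1 plus a negative binomial count of size 1. Many zeros and a long right tail follow from these assumptions; the article does not describe the distribution.

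**Rejection under no effect, nominal 0.05** (20,000 runs for the 2×2 forms, 1,000 for the others):

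| Form of test | Rejection rate |
|---|---|
| Any versus no hospital day, per patient | 0.045–0.057 |
| Cross-tabulation of distinct day values, per patient | 0.000–0.010 |
| Mann-Whitney on days per patient (comparator) | 0.035–0.061 |
| Hospital days pooled over all patients, by arm | 0.47–0.71 |

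**Why the cross-tabulation hardly ever rejects.** With equal arms, a day value seen in one patient has expected count 0.5 in each arm. It adds (1 − 0.5)²/0.5 + (0 − 0.5)²/0.5 = 1 to the statistic and 1 to the degrees of freedom, whichever arm the patient is in. Such rows carry no information on the arms. In the simulation about 83–96% of day-value rows had expected counts below 5.

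**Rejection when stays differ.** Admission is 30% in both arms and mean stay is 14 versus 7 days, so mean days per patient are 0.3 × 14 = 4.2 versus 0.3 × 7 = 2.1.

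| Test | 37 per arm | 50 per arm |
|---|---|---|
| Any versus none, chi-square | 5.5% | 5.7% |
| Cross-tabulation, chi-square | 0.2% | 0.4% |
| Mann-Whitney | 6.3% | 7.3% |
| Permutation test of mean days | 19.7% | 24.3% |

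The permutation figures rest on 600 runs, so the 95% simulation margin is about 1.96 × √(0.2 × 0.8/600) = 3 percentage points. The any/none test stays near 5% because its own null hypothesis, equal admission, is true here.

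**The case against.** The strongest reply is that the natural use of a chi-square test here is any versus no hospital day, and that this form is statistically valid. That stands: its type I error is about 0.05. The defect on this reading is lost information and a mismatch with the stated research question.

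The power example also isolates length of stay. If case-management worked by preventing admissions, the any/none test would respond to it; no such scenario was simulated. And no method does well: even the permutation test reaches only 20–24% for a halving of stay, and Mann-Whitney 6–7%. Both points stand and limit how much the change can gain.

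A reader might infer three stronger things that the article does not support.

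- **That false positives will be common.** Type I error of about 0.5–0.7 arises only if days are pooled across patients and treated as independent. The article speaks of the patient's days and never mentions pooling.
- **That the economic evaluation is damaged.** It costs hospitalizations from the diaries, bootstraps the cost difference and describes volumes of care by arm. It takes nothing from this test.
- **That unequal follow-up has been overlooked.** A condensed article may leave this to the full protocol or analysis plan, so its absence here is no finding.

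**Conclusion.** The stated test does not match the stated outcome, and this rests on the text alone. Used per patient, the chi-square test either ignores the number of days while holding its type I error near 0.05, or treats day counts as unordered labels and rejects in at most about 1% of trials. In the example with equal admission and mean stay 14 versus 7 days, this means 5–6% or under 1% rejection, against 20–24% for a permutation test of mean days. Those sizes depend on the assumed admission rates and stays; the mismatch does not.

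The point deserves correction but is limited in reach. Hospital days is the last-listed secondary outcome, and the primary outcome, sample size and economic evaluation are unaffected.

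**What to change.** Under Analysis – Effect evaluation, replace the chi-square test for hospital days by a per-patient comparison of mean hospital days between arms, using a permutation test or a bootstrap confidence interval for the difference. Bootstrapping is already planned for costs under Analysis – Economic evaluation. If the proportion of patients with any admission is also of interest, define it as a separate outcome and keep the chi-square test for that.

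The cost is one sentence and no new data. Power will remain low with about 100 participants, so the estimate and its interval should carry the report. The percentile bootstrap may be slightly liberal: with 37 per arm, in a null simulation with similar assumed inputs, it rejected in 5.6–7.8% of trials. That favours the permutation test for the p-value and the bootstrap for the interval.

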**Effect evaluation: secondary outcomes**				
b. Quality of life of the caregiver	SF-36 [48]	X	X	X
	EQ 5-D [57]	X	X	X
c. Psychological well-being of the caregiver	CES-D [49]	X	X	X
d. Caregiver's burden	SPPIC [50]	X	X	X
e. Days until institutionalization of the patient	GP	continuous registration		
f. Quality of life of the patient	DQOL [51]	X	X	X
	EQ 5-D [57]	X	X	X
g. Days until death of the patient	GP	continuous registration		
h. Hospital days of the patient	Cost diaries	continuous registration		

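### Patient quality of life (DQOL) is assigned a Student t-test although a pre-randomization DQOL score is available; the test is valid but less precise than the baseline-adjusted linear model already planned for the caregiver scales

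*Protocol article*

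**What the plan says.** The Analysis section (Effect evaluation) of the protocol article names methods outcome by outcome. It opens with the linear model: "General Linear Models are used to analyze differences between the intervention and usual care group on caregiver's sense of competence", and the same sentence adds caregiver quality of life and caregiver psychological well-being. Next comes "Potential baseline differences are accounted for by covariates". After a sentence on Cox models for time to institutionalization and death, two patient outcomes are taken together: hospital days and "patient's quality of life are tested by a chi-square test and student t-test, respectively". The paragraph closes with "Potential confounding is checked, including the effect of different interviewers and nurses".

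The list of outcomes under Measurements defines the patient outcome: "Patient's quality of life as measured with the Dementia Quality of Life Instrument (DQOL)". Table 1 marks it at all three visits: "f. Quality of life of the patient DQOL [51] X X X". The visit times are given in Measurements: "At baseline (T0), and after 6 (T1) and 12 months (T2) trained interviewers visit participants". The Randomization section places allocation after the baseline measurement, so the T0 score is a true pre-randomization value.

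Table 1 also lists the EQ-5D for the patient. That instrument supplies the utilities of the economic evaluation; this point concerns the DQOL.

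**The concern.** DQOL is a scale score with a baseline value, like the caregiver scales beside it, yet it is the one assigned a test that takes no covariate. No reason is given.

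In a randomized comparison of a scale score, the baseline value of the same scale is usually among the strongest predictors of the follow-up value. Leaving it out has two costs. Variation between patients that baseline would explain stays in the error term, so the confidence interval is wider than it needs to be. And if the arms happen to differ at baseline, part of that difference passes into the estimated effect.

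Both costs matter more in a small trial. The Discussion describes the sample of about 100 as relatively small, expects heterogeneity, and says that it cannot be enlarged. Baseline adjustment is one of the few sources of precision left. What is at stake is the precision of one secondary outcome, which is named in the secondary research question. The primary analysis on sense of competence is not touched.

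**Working it through.** **Inputs from the article.** Sample size calculation: α = 0.05, power 0.80, SCQ mean 17.9, SD 5.2, range 4–27, anticipated difference 15%, 37 per group, dropout about 25%, total 100. Table 1: DQOL at T0, T1 and T2.

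**Assumptions.** The article gives no SD, effect or baseline-to-follow-up correlation r for DQOL. I take r = 0.3, 0.5 and 0.7, express differences in DQOL SD units, use a two-sided test (sidedness is not stated), and borrow 37 per arm as the number of patients with an evaluable DQOL.

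**1. The plan's own figure.** 15% of the 23-point SCQ range is 0.15 × 23 = 3.45 points, and 3.45 / 5.2 = 0.663 SD. A two-sided t-test at 80% power needs 36.65, rounded up to 37 per group (power at 37: 0.804). With dropout, 37 / 0.75 = 49.3, so 50 per group and 100 in total. The stated figures reproduce. They concern the SCQ, and only the 37 is carried forward.

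**2. Final-score t-test against baseline adjustment.** In units of σ², the variance of the group difference is

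- final-score t-test: 2/n
- linear model with baseline: (2/n)(1 − r²)

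With n = 37, the t-test has a standard error of √(2/37) = 0.2325 SD, and the difference detectable at 80% power is 0.66 SD. Adjustment multiplies this by √(1 − r²). The single degree of freedom spent on the covariate is ignored.

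| r | 1 − r² | variance cut | √(1 − r²) | detectable difference | equivalent n per arm, 37/(1 − r²) |
|---|---|---|---|---|---|
| t-test | 1 | – | 1 | 0.66 SD | 37 |
| 0.3 | 0.91 | 9% | 0.954 | 0.63 SD | 40.7 |
| 0.5 | 0.75 | 25% | 0.866 | 0.57 SD | 49.3 |
| 0.7 | 0.51 | 49% | 0.714 | 0.47 SD | 72.5 |

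**3. Change-score t-test.** The article does not say whether the t-test is on final or change scores. With equal SDs at both visits, the variance factor for change is 2(1 − r). The excess over adjustment is

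2(1 − r) − (1 − r²) = (1 − r)²,

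which is positive for every r below 1.

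| r | change score, 2(1 − r) | adjusted, 1 − r² | ratio, 2/(1 + r) |
|---|---|---|---|
| 0.3 | 1.40 | 0.91 | 1.54 |
| 0.5 | 1.00 | 0.75 | 1.33 |
| 0.7 | 0.60 | 0.51 | 1.18 |

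Below r = 0.5 the change-score test is also less precise than the final-score test, whose factor is 1.

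**4. Chance imbalance, final-score reading.** The baseline difference between arms has standard error 0.23 SD, with a 95% range of ±1.96 × 0.2325 = ±0.46 SD. A fraction r of it carries into the final-score difference. At the 95% limit this is 0.3 × 0.456 = 0.14, 0.5 × 0.456 = 0.23 or 0.7 × 0.456 = 0.32 SD.

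**The case against.** **The t-test is valid.** This stands. Under randomization it is unbiased on average and keeps its type I error. A reader might infer that the patient result would be biased or wrong; the documents do not support that. The cost is in precision and in how far a single realized estimate can be moved by chance imbalance.

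**The t-test may not ignore baseline.** This also stands. A reader might infer that the T0 score is certainly unused, but the article states neither the score type nor the visit for this test, and a change-score test would use T0. Step 3 shows that the loss of precision remains under that reading, though it is smaller at high r.

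**Other sentences may already bring in adjustment.** The covariate sentence is not expressly limited to the caregiver outcomes, and the confounding check comes directly after the t-test. So the t-test may not be the only look at this outcome. But a t-test takes no covariate, neither sentence names baseline DQOL, and adjusting only after a check is not a prespecified analysis.

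**Detail may be left to a fuller plan.** That would answer a gap. Here the article names the test, so the choice can be reviewed as stated.

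**The gain may be small.** At r = 0.3 it is: 9% of variance. Nothing in the article rules out such a value. Decline is progressive, and a caregiver may complete a questionnaire when the patient cannot.

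**Power for DQOL cannot be quoted.** A reader might take a power for this outcome from the sample size section. 15% of the SCQ mean over its SD is 2.685 / 5.2 = 0.516, which gives 59% power at 37 per group. But the effect belongs to the caregiver scale, and that reading does not even reproduce the 37 (it needs 60 per group). The range reading gives 0.663 and 80%. Neither is a DQOL figure.

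**Conclusion.** The point holds as one of efficiency on a secondary outcome. The article fixes a method for DQOL that is valid but less precise than the baseline-adjusted model it plans for three caregiver outcomes, and the baseline score needed is already being collected before randomization.

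Against a final-score t-test, adjustment saves 9, 25 or 49% of the variance at assumed r of 0.3, 0.5 or 0.7. The detectable difference at 37 per arm moves from 0.66 SD to 0.63, 0.57 or 0.47 SD. Against a change-score t-test the saving is different in size but present for every r below 1. The direction needs only a non-zero correlation in the first case and r below 1 with equal SDs in the second. The size rests on r, which the article does not give, and on 37 patients per arm having an evaluable DQOL, a number derived for the caregiver scale.

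The change is worth making, but the article's primary conclusion does not depend on it.

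**What to change.** In the Analysis section, take patient quality of life out of the t-test sentence. State instead that 12-month DQOL is analyzed with a General Linear Model on arm, with baseline DQOL as a covariate fixed in advance, and that the adjusted difference is reported with its 95% confidence interval.

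The cost is one sentence and one degree of freedom. No new data or visits are needed.

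A practice term (the blocking factor) and a joint model of the 6- and 12-month scores are optional and not part of this fix. The article states neither for the caregiver outcomes. The number of practices is not given, so a practice term could use many degrees of freedom with about 2 × 37 = 74 completers.
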